### Data Collection

Patient data will be collected and collated by the research assistants and postdoctoral research fellows using standardized electronic (REDCap) data collection forms.

### Precohort (Retrospective Data Collection)

Data will be collected from Health Information Management System to identify patients who are readmitted within 30 to 90 days. Re-presentation data for the ED will require data collection from Cerner FirstNet, as *ICD-10* codes are not used at the ED sites of the participating hospital. Sociodemographic characteristics, such as age, sex, height, weight, and Aboriginal and/or Torres Strait Islander status; clinical characteristics, such as current medications, medication history, comorbidities, laboratory results (ie, full blood count, renal function tests, liver function tests, coagulation studies, lipid levels, etc), and the Charlson Comorbidity Index; and hospitalization characteristics, such as length of stay, presenting complaint, ward location, cost of admission, and any associated events (readmissions, hospital-acquired complications, or other), and treating team will be compiled using available electronic sources and digital health records. These data will be extracted using hospital reporting systems such as the Hospital Based Corporate Information System and the integrated electronic medical record.

### Postcohort (Prospective Data Collection)

Research staff will use standardized data collection forms to collect the activities that were delivered to patients during the intervention. The same variables will be collected in both the preperiods and postperiods to enable direct comparison of results. Collected data will include sociodemographic, clinical, hospitalization characteristics, and costs associated with the admission of interest and any associated events (readmissions, hospital-acquired complications, or other).

### Data Management

Data will be collected at the sites using standardized electronic (REDCap) data collection forms. REDCap data are encrypted in transit and storage and require 2-factor authentication. REDCap is a secure application that will enable data sharing between Queensland Health (QH) sites. Data will also be stored electronically in a safe and secure manner on a password-protected secure drive on the QH server and/or on the University of Queensland (UQ) Research Data Manager (RDM) server. Deidentified data and statistical analyses can be accessed with appropriate ethics and governance approvals through the UQ RDM system.

The UQ RDM is an access-controlled, authenticated network computer drive managed by Information Technology Services. Trial data will be stored after completion for a minimum of 7 years.

### Trial Monitoring

The RECARD program has a Program Steering Committee (PSC) and an Expert Advisory Board (EAB) to which any issues or concerns can be escalated from the research team. In the event of any potential adverse events, these will be managed at each site as per their local care procedures and within QH guidelines. The trial has also been registered, and a review of safety reports will be maintained as a standing agenda item for the PSC meetings so that any questions or concerns can be raised regularly and consistently. To enable optimal safety and harm reporting, there will also be 3 external clinicians who are independent of the RECARD trial team, the PSC, and the EAB, who will act as safety monitors. They will be provided with readmission reports for the intervention period related to cardiac readmissions to each hospital. Trends for readmissions (starting 3 months prior to implementation of the new service model [poststudy]) will be monitored, and any rise potentially attributable to the new model of care will be further investigated at the relevant site.

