## Introduction

### Background

The transition from hospital to primary care is a high-risk period for patients due to complex communication among multiple health care professionals, frequent medication changes, and complex care plans [1]. These factors increase the likelihood of medication harm and hospital readmission [2]. Implementing a structured transition of care (TOC) service with tailored support may help mitigate these risks [3,4].

Cardiovascular disease remains one of the leading causes of mortality in Australia and is managed with high-risk medications, such as anticoagulants and antiplatelets, that require careful titration [5,6]. These medications are a major contributor to medication harm, leading to medication-related hospital readmissions, morbidity, and mortality [5]. Associated complications include bleeding, acute kidney injury, hypotension-related falls, and electrolyte disturbances. Patients recovering from acute myocardial infarction (AMI) or cardiothoracic surgery (CS) are particularly vulnerable [6,7]. A previous study by the authors found that 6% (94/1564) of post–myocardial infarction patients were readmitted due to severe medication harm [5]. Another Australian study reported that 93% of cardiology unit discharges involved at least one medication-related problem, often linked to uncertainty about medications, drug interactions, and adverse effects [8].

Health inequities further exacerbate adverse cardiovascular outcomes. A dedicated TOC practitioner, trained in medication management, who can advocate for and provide timely navigation for patients as they return to the community remains a significant gap for some of these specialized high-risk patient groups [9]. For instance, in Queensland, hospital programs such as Better Cardiac Care for Aboriginal and Torres Strait Islander teams have improved aspects of medication management, such as ensuring medication supply and improving discharge communication [7,10-13]. Systemic inequities, treatment complexity, and limited access to culturally safe or patient-tailored services likely heighten risks, necessitating tailored, co-designed TOC interventions, as we propose.

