### Description of the TOC Service Model and Activities in the Bundle of Care

TOC services have many steps at which communication between patients and clinicians can occur (Figure 3). Table 1 highlights the potential touchpoints in the patient journey where various activities are provided to intervention participants as part of the TOC service. Typical activities delivered throughout a patient’s inpatient stay and in the postdischarge setting are described below [34]. The clinical skill set of NPs allows them to modify medication dosing, provide pathology requests, undertake patient observations, and interpret patient symptoms. In collaboration with the TOC pharmacist, the NP will run a 1-day-per-week clinic for patients who have specific comorbidities, pathology, physiology, or electrolytes requiring follow-up and patients with newly prescribed, withheld, or dose changes to β-blocker and angiotensin-converting enzyme inhibitor/angiotensin receptor blocker medications.

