### Outcome Measures

#### Primary Outcome: Medication-Related Hospital Readmissions and Causality Analysis

All patients who are readmitted to the hospital within 30 days following discharge from the PAH, RBWH, or TUH will be retrospectively reviewed to identify whether their readmission was medication-related.

For the primary outcome of 30-day medication-related hospital readmissions, cases will be confirmed and validated using a bimodal approach. The first will include the use of *International Statistical Classification of Diseases and Related Health Problems, Tenth Revision, Australian Modification* (*ICD-10-AM*) “Y” codes to determine “drugs, medicaments and biological substances causing adverse effects in therapeutic use.” The second approach will involve the review of the patient discharge summary, progress notes, and laboratory markers by 2 senior pharmacists to confirm 30-day medication-related readmission.

Finally, an expert panel comprising a senior pharmacist, specialist nurse, cardiologist, and researcher will independently review readmissions to reach a final consensus. The expert panel will confirm medication-related hospital readmissions by assessing causality using tools such as the Naranjo algorithm or the World Health Organization Uppsala Monitoring Centre criteria.

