### Organization Structure of the Trial

The Program Management Committee (PMC) will oversee the trial on behalf of the sponsor (the sponsor retains ultimate responsibility for the trial). The PMC is focused on operational matters regarding the trial management. The PMC will provide regular reports to the PSC, such as information on study status, protocol compliance, budget, data management, legal or regulatory issues, and risk management and mitigation.

The PSC will oversee the conduct and integrity of the RECARD trial and will provide support to the PMC. The PSC is responsible for the execution of all activities, including trial design, finalization of the protocol, intervention delivery, data collection, data management, data analysis, report writing, milestone reporting, and results dissemination. An important function is to support risk management and provide status reports to the EAB.

The EAB comprises international experts who will provide oversight and advice to the PSC in relation to the RECARD trial. The UQ School of Pharmacy and Pharmaceutical Sciences is the coordinating faculty on behalf of UQ.

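### The only feed named for the independent safety monitors is cardiac readmissions, which on a plain reading leaves out the medication harms that the protocol itself lists

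*Protocol article*

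**What the plan says.** The Trial Monitoring section of the protocol article gives the reason for independent monitors: "To enable optimal safety and harm reporting, there will also be 3 external clinicians". They are described as independent of the trial team, the Program Steering Committee (PSC) and the Expert Advisory Board. The section then states what they will receive: "They will be provided with readmission reports for the intervention period related to cardiac readmissions to each hospital". The next sentence reads "Trends for readmissions (starting 3 months prior to implementation of the new service model [poststudy]) will be monitored", and adds that a rise that might be due to the new service will be looked into at the site concerned. That sentence does not use the word cardiac, and it does not say who watches the trends.

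The Background names the harms of the medicines involved: "Associated complications include bleeding, acute kidney injury, hypotension-related falls, and electrolyte disturbances". The description of the service model says "The clinical skill set of NPs allows them to modify medication dosing". Under the primary outcome, all patients readmitted within 30 days "will be retrospectively reviewed to identify whether their readmission was medication-related", with no restriction to cardiac diagnoses.

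Two other safety routes are described. Adverse events are handled at each site under local procedures, and "a review of safety reports will be maintained as a standing agenda item for the PSC meetings".

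**The concern.** The monitors are the only group in the plan that is described as independent and has safety as its task. The service works through medication management and includes dose changes, so the harm it could plausibly cause is medication harm. A patient readmitted with a bleed, kidney injury, a fall from low blood pressure or an electrolyte problem need not carry a cardiac diagnosis. If the monitors' report is filtered on cardiac diagnosis, they would be looking at a different set of events from the one in which such harm would show.

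At stake is whether a rise in medication harm during the intervention period would come to independent attention in time to act on it. The validity of the final effectiveness comparison is not affected.

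**Working it through.** No figure in the plan decides this point, so the check sets the relevant sections side by side.

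1. **Scope of the monitors' feed.** Trial Monitoring: readmission reports for the intervention period, concerning cardiac readmissions, by hospital. The term is not defined.
2. **Scope of the harms named.** Background: four complications. Taken one at a time (bleeding, kidney injury, falls, electrolyte disturbance), none is in itself a cardiac diagnosis. Count: 4 of 4 fall outside a feed defined by cardiac diagnosis, unless the readmission is also classed as cardiac for another reason.
3. **Scope of the primary outcome.** Primary Outcome section: every 30-day readmission is reviewed for a medication cause. The feed in step 1 is narrower than this and omits the non-cardiac part.
4. **Could the service plausibly produce these harms?** The service model section gives nurse practitioners scope to change doses. It describes a weekly clinic for, among others, patients with electrolytes to follow up or with new, withheld or changed β-blocker and ACE inhibitor/ARB treatment. The link to the harms in step 2 is direct.
5. **Do the other routes give independent sight during the trial?**
   - *Local management of adverse events:* no onward report to the monitors is stated.
   - *Safety reports to the PSC:* the content is not described and could include non-cardiac events. But the Organization Structure section says "The PSC is responsible for the execution of all activities, including trial design, finalization of the protocol, intervention delivery", so the PSC is not independent of the service.
   - *Readmission trends:* not expressly cardiac, but the person or group who monitors them is not stated.
   - *Primary-outcome review:* covers all readmissions but is retrospective. The Results section says that no preliminary analysis has been undertaken and that analysis is planned for January to March 2027, after recruitment ends in November 2026.
   - *All-cause readmissions at 30, 60 and 90 days, and Y-coded readmissions at 60 and 90 days:* these are study outcomes, and the article does not say that they go to the monitors.
6. **Are the data at hand?** Yes. The data collection sections identify readmissions within 30 to 90 days and collect the same variables in both periods. Y codes are already used for the primary outcome and for the 60- and 90-day outcomes.

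Result: on a plain reading of step 1, no stated route brings non-cardiac medication harm to the independent monitors while patients are still being treated.

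**The case against.** The strongest reply is that the restriction is partly inferred. The article does not say that the monitors receive nothing else, and the trends sentence is not limited to cardiac events. The term could also mean readmissions of the cardiac cohort, for any reason. This stands, and it limits the point to what is named. It does not remove the point: whoever prepares the report could reasonably filter by diagnosis, so the wording needs correcting on either reading.

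A second reply is that report content usually sits in a monitoring charter or full protocol. That would answer a complaint about missing detail. Here the article states the content of the feed, and the objection is to what is stated.

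Two stronger readings are tempting and are not supported.

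- *A reader might infer that these harms would go undetected.* They would not. The PSC may see them in safety reports, and the outcome review covers every 30-day readmission. What may be lacking is independent sight of them during the trial.
- *A reader might infer that trends starting 3 months before implementation give too noisy a baseline.* A calculation can be made: 2211/4 ≈ 553 patients. Split by the recruitment shares of 159/343, 131/343 and 53/343, this gives about 256, 211 and 85 patients per site. At 7%, that is about 18, 15 and 6 events, with exact 95% Poisson intervals of 10.7–28.4, 8.4–24.7 and 2.2–13.1. Doubled counts of 36 and 30 lie outside the intervals at the two larger sites; only at the smallest does a doubling to 12 lie inside. The inputs are also unsuitable. The 7% is the medication-related rate, not the rate of cardiac or all-cause readmission, which the article does not give. The shares appear to describe patients recruited to the service, not all discharges. A recent run-in is also a reasonable comparator, since the precohort ended in June 2024, about 17 months before the December 2025 start.

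**Conclusion.** The point holds as a mismatch within the protocol article. The feed named for the independent monitors, read as readmissions with a cardiac diagnosis, is narrower than the harms listed in the Background (4 of 4 are not in themselves cardiac) and narrower than the primary outcome. Non-cardiac medication harm may therefore not reach the independent monitors during the trial, although it could reach the PSC and would appear later in the outcome data.

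This rests on two assumptions: that cardiac refers to the readmission diagnosis, and that no other feed to the monitors exists in documents not shown. The number of events affected cannot be estimated from the article. The point concerns safety oversight; the sample size, the primary analysis and the care given are untouched. Recruitment runs to November 2026, so a change can still serve participants.

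**What to change.** Amend the sentence in Trial Monitoring so that the monitors receive all-cause 30-day readmissions of study patients, by site, with two subsets shown separately: those carrying an ICD-10-AM Y code, and cardiac readmissions. State what counts as a cardiac readmission, and say who monitors the readmission trends. Showing the 12-month precohort beside the 3-month run-in is optional.

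The cost is a longer report for three people to read and some extra work in preparing it. The data are already being collected. The Y-coded column can be filled only once a readmission has been coded, and the article does not say how long that takes; this is one reason to show the all-cause count beside it.

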**Results:**

The predata are currently being collected for patients discharged from the 3 hospital sites during the 12-month prestudy period. The postdata intervention began on December 10, 2025. As of May 27, 2026, a total of 343 patients have been recruited at the 3 study sites.

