### Sample Size

It is expected that, under conditions of usual care, the rate of medication-related hospital readmissions within 30 days among patients discharged following an AMI is 7% [40]. Interventions have reduced this rate from 7% to 4.9% (an absolute risk reduction of 2.1%) [41]. As mentioned previously, only a subset of the population (those identified as being at highest-risk based on model scoring and/or clinician referral) will be targeted to receive the intervention. Guided by previous studies and resources, we expect to prioritize the top 25% of patients at high-risk of medication-related readmission [42]. An additional 10% of patients are expected to be referred by the treating team. However, the final proportion of patients who will be triaged for intervention will be guided by a local audit following the development of the risk model. Because the high-risk patients will likely have a higher rate of potential readmission (ie, >7%), we expect that an intervention applied to only this group will still produce an absolute risk reduction of at least 2.1% averaged across the entire intervention sample, even though we expect the risk in the low-risk group to remain unchanged. Therefore, the sample size calculation is based on the overall sample required, not just the high-risk group.

Assuming a baseline risk of readmission of 7% and a significance level of .05, a sample size of 1990 participants is required in both the prestudy and intervention periods (ie, a total of 3980 patients across both prestudy and intervention periods) to detect an absolute risk difference of 2.1% with a power of 0.80. We assume a minimal dropout and refusal rate of 10%; taking this into account, we aim to recruit 2211 participants into each 12-month period (a total of 4422 participants across both the prestudy and intervention periods). We expect 35% of patients (~775 patients) to be flagged as high risk, consent to the study, and be given the TOC intervention. The remainder of the patients enrolled in the study will be given usual care as described earlier. Delivering the TOC service to 775 participants across the study sites over 12 months is both logistically feasible and achievable.

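### The safety trend uses a 3-month, season-unmatched lead-in and does not separate service recipients, so it discriminates poorly between harm and noise

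*Protocol article*

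**What the plan says.** The Trial Monitoring section appoints three external clinicians, independent of the trial team and both committees, as safety monitors. Their material is described in one sentence: "They will be provided with readmission reports for the intervention period related to cardiac readmissions to each hospital". The section then sets the baseline: "Trends for readmissions (starting 3 months prior to implementation of the new service model [poststudy]) will be monitored". The trigger for action, which is left to local follow-up, reads as follows: "any rise potentially attributable to the new model of care will be further investigated at the relevant site". No threshold, test or reporting interval is given.

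The same section keeps another route open: "a review of safety reports will be maintained as a standing agenda item for the PSC meetings". Concerns can also be escalated to the Program Steering Committee and the Expert Advisory Board.

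Two facts from elsewhere fix what the trend can show. The abstract gives the start date: "The postdata intervention began on December 10, 2025". The Sample Size section gives the share treated: "We expect 35% of patients (~775 patients) to be flagged as high risk, consent to the study, and be given the TOC intervention". It expects risk in the remaining patients to stay unchanged, and expects recipients to have a rate above the average.

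**The concern.** The section states two features, and both weaken the trend.

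- **Season.** A lead-in of about September 10 to December 9, 2025 meets the same calendar dates again only in the last quarter of a service that runs to November 30, 2026. Until then, any change from the lead-in mixes the service with the time of year. The window also lies outside the historical cohort (July 2023 to June 2024), so the trial's own pre-period data do not cover it.
- **Dilution.** Reports are by hospital and are not described as separating recipients. If they cover the trial population, about 65% of the patients behind them never receive the service. A rise confined to recipients is then watered down and cannot be told apart from one in usual care.

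At stake is how useful the trend is to the only reviewers described as independent of the trial team and its committees. A short, noisy baseline gives them either a signal too weak to stand out or alarms that carry little information.

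**Working it through.** **Inputs from the Sample Size section.** 2211 patients per 12 months; 35% recipients; "Assuming a baseline risk of readmission of 7% and a significance level of .05". These figures reproduce: 7% v 4.9%, two-sided 5%, 80% power gives 1990.8 per period (stated 1990); 1990/0.90 = 2211; 0.35 × 2211 = 774 (stated about 775). The article gives no operating characteristic for the safety trend, so there is no monitoring figure to reproduce.

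**Assumptions.**
- The 7% medication-related rate stands in for the cardiac readmission rate, which the article does not give.
- The three sites are equal.
- The reports cover the trial population.
- Recipients carry a share s of events between 50% and 70%. This implies recipient rates of 0.50 × 7%/0.35 = 10% to 0.70 × 7%/0.35 = 14%, in line with the expectation of more than 7%.

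**Volumes.** One site-quarter: 2211/(3 × 4) = 184 patients, of whom 0.35 × 184 = 64 are recipients. All sites: 2211/4 = 553 in 3 months and 1106 in 6 months.

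**Dilution.** Hospital rate after a relative rise RR in recipients: p1 = p0 × [1 + s(RR − 1)]. For RR = 1.5:
- s = 0.50: 7% × 1.25 = 8.75%
- s = 0.70: 7% × 1.35 = 9.45%

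A 50% rise in recipients is therefore a 25-35% rise in the hospital figure. In counts, 184 × 7% = 12.9 events becomes 16.1 to 17.4.

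**If a test were applied (one-sided 5%, normal approximation).** Power = Φ[(p1 − p0 − 1.645 × SE0)/SE1], where SE0 uses the pooled rate and SE1 the two separate rates. For one site, 184 v 184:
- 8.75%: both SEs 0.0281; (0.0175 − 0.0462)/0.0281 = −1.02, so 15%
- 9.45%: both SEs 0.0286; (0.0245 − 0.0471)/0.0286 = −0.79, so 21%

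The same formula gives:

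| Comparison | RR 1.5 | RR 2 |
|---|---|---|
| One site, 3 v 3 months (184 v 184) | 15-21% | 32-48% |
| Pooled, 6 v 3 months (1106 v 553) | 33-51% | 76-94% |
| Pooled, 6 v 12 months (1106 v 2211) | 56-79% | 96% or more |

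Sensitivity, one site-quarter, RR 1.5: 13-18% at a 5% base rate and 25-37% at 15%. If RBWH's share of recruits so far (53/343) held for all its patients, it would have 53/343 × 2211/4 = 85 per quarter, and power would be 11-14%.

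**If the trigger is read literally as any rise.** The chance that the later rate is simply higher is Φ[(p1 − p0)/SE1]:
- 8.75%: Φ(0.0175/0.0281) = Φ(0.62) = 73%
- 9.45%: Φ(0.0245/0.0286) = Φ(0.86) = 80%
- no effect: Φ(0) = 50% per site

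For at least one of three sites: no effect, 1 − 0.5³ = 88%; with the rise, 1 − 0.27³ = 98% to 1 − 0.20³ = 99%. The alarm is nearly as likely without harm as with it.

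**Limit of the 12-month figure.** It uses all 12 lead-in months, so season would need adjustment. Strict matching of the six service months to the same six months a year earlier is 1106 v 1106. Then (0.0175 − 1.645 × 0.01145)/0.01145 = −0.12, or 45%, and (0.0245 − 1.645 × 0.01168)/0.01167 = 0.45, or 67%. That still exceeds 33-51% and removes the seasonal mismatch.

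**The case against.** The strongest reply is that the section sets no test and no quarterly site look. Clinicians are to judge any potentially attributable rise, and naming the relevant site says where a signal is investigated, not how the data are displayed. This stands. A reader might infer from the power figures that a serious rise would mostly go undetected; the document does not support that, because under its literal trigger such a rise would usually show. What the figures support is poor discrimination.

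Other stronger readings also fail.

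- **Whole-hospital readmissions.** The reports concern cardiac readmissions. Whether they are limited to index AMI and surgical patients is not said; if they are not, dilution is worse than computed.
- **The only harm check.** Safety reports also go to every Program Steering Committee meeting, and adverse events are handled locally.
- **Monitors left without a baseline**, because reports are for the intervention period. The next sentence starts the trend 3 months earlier.
- **Investigation of the wrong site.** The reports count readmissions to a hospital, whereas the primary outcome follows discharge from one. No frequency of cross-site readmission is given, and an investigation could be expected to notice the index hospital. This is minor.

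It can also be said that a condensed article leaves monitoring detail to the full protocol. That excuses the missing threshold and reporting interval. It does not excuse the 3-month start and the by-hospital reports, which the article states.

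**Conclusion.** The point holds as a design weakness in a safety safeguard; it does not touch the primary analysis. The seasonal mismatch follows from the stated dates alone. The dilution follows from the 35% share if the reports cover the trial population without separating recipients. Its size rests on the assumed 7% rate, equal sites and 50-70% of events in recipients: a 50% rise in recipients becomes 25-35% at hospital level. One site-quarter would detect that with 15-21% probability under an assumed one-sided 5% test. Under the literal trigger it would show 73-80% of the time, against 50% with no effect. The base rate and site size move these figures but do not change the conclusion for a 50% rise at one site. An improvement is worthwhile because it is cheap and recruitment runs to November 2026.

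A reader might also expect a recipients-only comparison with a pre-service baseline to solve the problem; a calculation of 387 v 774 patients gives 79-91%. That figure should not be relied on. It needs a pre-service group of comparable risk, whereas recipients are selected by model score or clinician referral, and a recipient flag exists only after go-live.

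**What to change.** In Trial Monitoring:

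1. Start the series at least 12 months before December 10, 2025, so that each service month can be set against the same calendar month, and state that the monitors receive this baseline.
2. Show recipients and usual-care patients as separate series during the service period. Note that they differ in risk by selection and should not be compared directly with each other.
3. Give the monitors a pooled, cumulative view as well as the site view, and list each readmission also by hospital of index discharge.

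Under the assumptions above, the longer lead-in raises pooled detection of a 50% rise at 6 months from 33-51% to 56-79% (45-67% with strict month matching). No recipients-only detection figure should be claimed unless a comparable-risk pre-service group can be scored.

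The cost is a longer extract from the hospital reporting systems already named under Data Collection, a recipient flag taken from the forms that record delivered activities, and a little programming. Patients undergo no additional procedures.
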